#### 9.2.2.3. Waist-hip ratio

Waist-hip ratio is used in combination with BMI to assess obesity and can be more accurate as BMI can be skewed by muscle mass [62]. The waist-hip ratio is the ratio of the circumference of the waist to that of the hips. This is calculated as waist measurement (to the nearest cm) divided by hip measurement (to the nearest cm). Measurements will be conducted at Visits 1 and 6 by a qualified member of staff who has signed/dated the staff delegation log and waist circumference, hip circumference and waist-hip ratio will be recorded directly into the CRF.

#### 9.2.2.4. Blood pressure

Blood pressure is usually expressed in terms of the systolic (maximum) pressure over diastolic (minimum) pressure and is measured in millimeters of mercury (mm Hg) via a non-invasive sphygmomanometer. Measurements will be conducted at screening, Visits 1, 6 and follow-up by a qualified member of staff who has signed/dated the staff delegation log and recorded directly into the CRF.

#### 9.2.2.5. Blood tests

Blood samples collected at screening, baseline, study Visits 3 (day 7), 4 (day 28), 6 (day 35) and follow-up (day 42 onwards) will be analysed immediately through the Leeds Teaching Hospitals NHS Trust Pathology Service or processed and stored for future research.

Blood samples at each of these visits will evaluate HbA1c (mmol/mol) and lipids [total and high density lipoprotein cholesterol and triglycerides (mmol/l)] for T2DM disease markers and FBC [haemoglobin (g/l), white cells and platelets ( $\times 10^9/\text{l}$ ), red cells ( $\times 10^{12}/\text{l}$ ), mean corpuscular volume (fl), haematocrit (%/100), mean corpuscular haemoglobin (pg), mean corpuscular hemoglobin concentration (g/l) and red blood cell distribution width (%)], LFT

[ALT, AST and gamma-glutamyl transpeptidase (iu/l), ALP (U/l), albumin (g/l) and bilirubin (umol/l)], eGFR (ml/min/1.73m^2), U+E [sodium, potassium and urea (mmol/l) and creatinine (umol/l)], adrenal [testosterone (nmol/l) and dehydroepiandrosterone sulphate (umol/l)] and thyroid [thyroid stimulating hormone (mIU/l) and free thyroxine (pmol/l)] function (AZD4017 safety markers). CK (iu/l) will also be measured at the screening visit. Samples will be collected by authorised research nurses.

Results will be sent to the CI or authorised delegated personnel for immediate monitoring signature and dating. Signed and dated result reports will be stored with the patient's medical notes for each visit and recorded in the CRF as pass or fail.

Blood will also be taken at baseline and day 35 for separation to serum and plasma and stored at -80°C in the WTBB designated storage area for plasma AZD4017 detection and future studies (up to 5 years). At 5 years after the end of the trial any residual samples will either be destroyed or placed in an approved Research Tissue Bank.

#### 9.2.2.6. Adverse event reporting

Any reported AE will record the following information directly into the CRF at Visits 2, 3, 4, 5 and 6

- Type of AE defined by the Common Terminology Criteria for Adverse Events (CTCAE) v5.0 preferred term
- Date of onset
- Severity (defined by CTCAE v5.0)
- Relation to study intervention (definite, probable, possible, unlikely, unrelated)
- Date of resolution

#### 9.2.3. Skin function

##### 9.2.3.1. Sudomotor function

The test is conducted using a Sudoscan device consisting of a simple desktop computer connected to two sets of large surface stainless steel electrodes: two for application of the palms, and two for the soles. The test will be conducted at Visits 1 and 6 and performed by the Scientific Lead at the SJUH Diabetes Centre. The procedure is non-invasive, pain-free and requires approximately 10min.

The patient places both hands and feet simultaneously on the designated electrodes and a painless scanning process ensues over the course of 2–3 min. A low voltage (1-4V) is incrementally applied to the electrodes, with the left and right electrodes serving alternatively as cathode and anode. At voltages <10V, the *stratum corneum* is electrically insulating; the sweat glands, however, consist of a cellular bilayer and therefore can transmit electrically charged ions to the electrodes through the skin's surface. The current of chloride ions generated is quantified and reflects C-fiber innervation. This chloride ion current is reported as electrochemical skin conductance measured in microSiemens (μS)

[48]. The results will be recorded directly into the CRF. Raw data on the Sudoscan device (including enrolment number, visit number and date) will be copied in its original form to secure server storage.

#### 9.2.3.2. Skin hydration

*Stratum corneum* hydration will be measured using a Corneometer CM 825 device. The device measures the change in the dielectric constant due to skin surface hydration changing the capacitance of a precision capacitor and can detect even slight changes in hydration (reported in arbitrary units).

The measurement will be taken at Visits 1 and 6 with a small portable probe that is applied to the skin, is non-invasive and pain-free. The test requires approximately 5min and will be conducted by the Scientific Lead. The results will be recorded in the CRF and stored as image files in a temporary folder (including enrolment number, visit number and date) on the secure (encrypted) laptop used for the measurements before transfer to a secure server.

#### 9.2.3.3. Epidermal barrier function

TEWL is a validated measure of skin epidermal permeability barrier function.

Evaporation of water from the skin occurs as part of normal skin metabolism. As barrier function is disrupted, water loss increases. The Tewameter TM 300 probe measures the density gradient of the water evaporation from the skin by two pairs of sensors (temperature and relative humidity) inside a hollow cylinder. The open chamber measurement method is the only method to assess the TEWL continuously without influencing its microenvironment. A microprocessor analyses the values and expresses the evaporation rate in g/h/m^2.

The procedure requires 5min to perform, is non-invasive, pain-free and will be conducted by the Scientific Lead at Visits 1, 2, 3, 4, 5 and 6. The results will be recorded in the CRF and stored as image files in a temporary folder (including enrolment number, visit number and date) on the secure (encrypted) laptop used for the measurements before transfer to a secure server.

#### 9.2.3.4. Epidermal barrier recovery

In addition to resting TEWL, epidermal function can be assessed by measuring TEWL recovery over time following barrier disruption by repeated tape stripping.

Following the initial TEWL measurement, adhesive patches (D-Squame tapes) will be used to gently remove the *stratum corneum* layers to a pre-specified TEWL rate from the lower inner forearm at Visits 1 and 4. Recovery of TEWL at this location will be evaluated by repeated TEWL readings at 3 hour, 48 hour and 7 days post-disruption at Visits 1, 2, 3, 4, 5 and 6.

This procedure will be conducted by the Scientific Lead and may cause a temporary mild discomfort or transient irritation which should subside within a few hours. The results will be recorded in the CRF and stored as image files in a temporary folder (including enrolment number, visit number and date) on the secure (encrypted) laptop used for the measurements before transfer to a secure server.

#### **9.2.3.5. Epidermal barrier integrity**

The number of tapes required is an indication of *stratum corneum* integrity. Tapes will be stored at -80°C in the WTBB designated storage area for future molecular biology studies. The results will be recorded directly in the CRF.

#### **9.2.3.6. Skin thickness**

Epidermal thickness will be evaluated by OCT at Visits 1 and 6 according to the manufacturer's instructions. Image files (including enrolment number, visit number and date) will be stored on the OCT machine until the end of the trial. They will then be transferred to a secure server, compiled, analysed and values for skin thickness entered into the CRF.

#### **9.2.3.7. Wound healing**

Both biopsies from visit 1 and two biopsies from visit 3 will be imaged by OCT at Visits 2, 3, 5 and 6. Recent studies suggest OCT may be a useful tool to evaluate wound re-epithelialization [63]. This imaging modality is already being utilised by our department [64]. OCT uses light to capture sub-micrometer resolution, three-dimensional images from within biological tissue (e.g. skin). The method is based on low-coherence interferometry, typically employing near-infrared light. The use of relatively long wavelength light allows it to penetrate 1-2mm into the tissue. In addition to wound diameter, collected images capture information on vascularization which may be used for future studies.

The procedure takes approximately 2min using a small probe applied to the skin, is non-invasive, pain-free and will be conducted by the Scientific Lead or delegated authorised personnel. Image files (including enrolment number, visit number and date) will be stored on the OCT machine until the end of the trial. They will then be transferred to a secure server, compiled, analysed and values for wound diameter entered into the CRF.

#### **9.2.3.8. RNA-seq gene expression profiling**

Freshly snap-frozen 3mm skin biopsies collected at Visit 1 and 4 will be used to examine differences in mRNA expression by RNA-seq between baseline measurement and following 35 days of AZD4017. Skin samples will be stored -80°C in the WTBB designated storage area until all samples have been collected prior to processing for RNA extraction and RNA-seq. Lists of expressed and differentially expressed genes will be stored on a secure sever (including enrolment number and visit number). Genes and pathways found to be regulated

by AZD4017 will be quantified by qPCR and the data (including enrolment number and visit number) will be stored on a secure server.

#### 9.2.4. Feasibility

Data for powering of secondary variables and feasibility of a future confirmatory trial will be captured on the CRF. Data on eligibility, recruitment, consent, randomization, adherence, retention and data completeness will be captured through a range of sources including eligibility, enrolment, screening and withdrawal logs, Informed Consent Forms, pharmacy records and diary cards (stored in the TMF) to enable assessment of future confirmatory trial feasibility.

## 10. STUDY PROCEDURES BY VISIT

### 10.1. Summary schedule of study assessments

Table 1. Summary schedule of study assessments

| Assessment (day)                   | Screening (-7 to -2) | Visit 1 (0) | Visit 2 (2) | Visit 3 (7) | Visit 4 (28) | Visit 5 (30) | Visit 6 (35) | Follow-up (>42) |
|------------------------------------|----------------------|-------------|-------------|-------------|--------------|--------------|--------------|-----------------|
| Eligibility                        | X                    |             |             |             |              |              |              |                 |
| Informed consent*                  | X                    | X           |             |             | X            |              |              |                 |
| ECG                                | X                    |             |             |             |              |              |              | X               |
| BMI, BP, waist-hip ratio           | BP only              | X           |             |             |              |              | X            | BP only         |
| Blood tests**                      | X                    | X           |             | X           | X            |              | X            | X               |
| 24 hour urine collection           |                      | X           |             |             |              |              | X            |                 |
| Skin hydration                     |                      | X           |             |             |              |              | X            |                 |
| Barrier function                   |                      | X           | X           | X           | X            | X            | X            |                 |
| Barrier recovery                   |                      | X           | X           | X           | X            | X            | X            |                 |
| Skin integrity                     |                      | X           |             |             | X            |              |              |                 |
| Sudomotor test                     |                      | X           |             |             |              |              | X            |                 |
| Biobank serum and plasma           |                      | X           |             |             |              |              | X            |                 |
| Randomization                      |                      | X           |             |             |              |              |              |                 |
| Tablet supply                      |                      | X           |             |             | X            |              |              |                 |
| 11 $\beta$ -HSD1 activity (biopsy) |                      | X           |             |             | X            |              |              |                 |
| RNA-seq                            |                      | X           |             |             | X            |              |              |                 |

|                                        |  |   |   |   |   |   |   |   |
|----------------------------------------|--|---|---|---|---|---|---|---|
| (biopsy)                               |  |   |   |   |   |   |   |   |
| Skin thickness                         |  | X |   |   |   |   | X |   |
| AE monitoring                          |  |   | X | X | X | X | X | X |
| Evaluation of biopsy site              |  |   | X | X | X | X | X | X |
| Wound healing                          |  |   | X | X |   | X | X |   |
| Compliance monitoring                  |  |   | X | X | X | X | X |   |
| AZD4017 in plasma and skin (biopsy)*** |  |   |   |   |   |   | X |   |

\* Informed consent will also be obtained prior to each biopsy

\*\* HbA1c, lipids, FBC, LFT, eGFR, U+E, adrenal and thyroid function (CK will also be analysed at screening). For further detail see section 9.2.2.5

\*\*\* Active (AZD4017) arm only after unblinding at the end of the trial

## 10.2. Screening visit (day -7 to -2) SJUH Diabetes Clinic

Patients invited to participate in the trial will be contacted by telephone after 72 hours and asked to confirm willingness to enrol, eligibility and identify a suitable study schedule. Two to seven days before the baseline visit (Visit 1), eligibility will be confirmed at screening by a medically qualified doctor and will be recorded in both the medical notes and CRF. Written informed consent will be obtained before testing for other exclusion criteria (clinically relevant acute ECG anomalies, hypertension and blood analyses). Potential participants will also be supplied with 24 hour urine collection devices. If all screening criteria are met, potential participants will be contacted by telephone when the results are ready to confirm enrolment and arrange a visit schedule.

## 10.3. Visit 1 (day 0) SJUH Diabetes Clinic and CAH LMBRU

Participants will return 24 hour urine samples for storage until processing. Participants will be asked if anything has changed since the previous visit.

**Baseline measures** will be conducted as follows: 1) BMI, BP, waist-hip ratio 2) skin hydration 3) epidermal barrier function and integrity 4) sudomotor function 5) blood samples for HbA1c, lipids, FBC, LFT, eGFR, U+E, thyroid and adrenal function and serum/plasma biobank storage 6) Randomization to 400mg oral AZD4017 twice daily or placebo 7) collection of IMP from pharmacy 8) obtain biopsy informed consent 9) 2 x 3mm biopsies for 11 $\beta$ -HSD1 activity RNA-seq 10) 3 hour barrier recovery time-point 11) skin thickness 12) payment

Pre-paid transport between SJUH and CAH for the skin thickness measurement will be arranged by a member of the trial team.

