### **6.4.2. Consent**

Assenting patients will then be invited to attend a screening visit where they will be formally assessed for eligibility and asked to provide written, informed consent. Where English is not the patient's first language every effort will be made to provide a Trust interpreter according to normal Trust procedures. The right of the patient to refuse consent without giving reasons will be respected. The original Informed Consent Form will be filed in the Trial Master File (TMF), with one copy given to the patient and one filed in the hospital notes. Consent pass or fail will also be recorded in the CRF. The written consent will be taken by an

eligible member of staff who has signed/dated the staff delegation log. The process of obtaining written consent will be clearly documented in the patient's medical notes.

A separate Informed Consent Form will be attained prior to the skin biopsy procedure which will be stored with the general Informed Consent Form in the TMF and recorded as pass or fail in the CRF.

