#### **6.5.2. Managing/replacing patients who withdraw early**

Participants who decide to withdraw will be invited to complete a withdrawal form which will be stored in the TMF (although refusal to do so will be respected). Participants who are withdrawn by the CI will be recorded in a Withdrawal Log that documents the enrolment number, participant initials, reason(s) for withdrawal and treatment offered (if applicable). A copy of the log will be retained in the CRF which will also directly capture information on withdrawal outcome (Discontinuation due to Adverse Event or Elective Withdrawal). Withdrawal Log originals will be stored in the TMF. Participants who withdraw or are withdrawn pre-randomization will be classified as screening failures (see section 6.3.4). Participants who withdraw or are withdrawn post-randomization (see section 6.5) will be classified as withdrawals and will not be replaced.

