### 8.2. Frequency and duration of the trial drugs

Participants will be randomised to receive either AZD4017 400mg twice daily (as close to 12 hours apart as possible) or placebo. AZD4017 or placebo will be dosed as 2 tablets orally twice daily for 35 days starting at the baseline visit (Visit 1).

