### 13.3. General statistical considerations

Unless otherwise specified, the last valid measurement before study medication administration will be utilized as the baseline value. In general, summary statistics [n (number of available measurements), arithmetic mean, standard deviation, median, minimum, and maximum] for quantitative variables and absolute and relative frequency tables for qualitative data will be presented.

Wherever possible the trial will be reported in accordance with the recommendations of the Consolidated Standards of Reporting Trials statement.

An initial blind review of the data will be completed prior to locking the database to identify patients to be excluded from per-protocol analysis.

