## 14.3. Subject information and informed consent

Before being enrolled in the clinical study, subjects must consent to participate after the nature, scope, and possible consequences of the clinical study have been explained in a form understandable to them.

A PIL that includes information about the study will be prepared and given to the subject at least 24 hours prior to the screening visit. This document will contain all the elements required by the ICH E6 Guideline for GCP and any additional elements required by local regulations. The document must be translated (by an independent interpreter) into a language understandable to the subject and must specify who informed the subject. Where required by local law, the person who informs the subject must be a physician.

During verification of eligibility, patients will be given the opportunity to ask questions and the nature and objectives of the study will be explained. A research nurse may help in this process but the study doctor is responsible for the General Informed Consent discussions at the Screening Visit. The Skin Biopsy Informed Consent at Visits 1 and 4 can be received by a qualified member of staff who has signed/dated the staff delegation log (i.e. study doctor or research nurse).

After reading the informed consent document, the subject must give consent in writing. The subject's consent must be confirmed at the time of consent by the personally dated signature of the subject and by the personally dated signature of the person conducting the informed consent discussions, (i.e. the study doctor for General Informed Consent or qualified research nurse for Skin Biopsy Informed Consent).

The original signed Informed Consent Form will be retained in the TMF. Other copies of the consent form are required:

- One copy will be kept in the patient's clinical notes
- One copy will be given to the patient

Consent is an ongoing process and will be reassessed at each study visit.

The Scientific Lead will not undertake any measures specifically required only for the clinical study until valid consent has been obtained.

The CI must inform the subject's GP about the subject's participation in the trial if the subject has a GP and if the subject agrees to the GP being informed.

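### Visit 1 randomises the patient and issues study drug before biopsy consent and the baseline biopsies, so a refusal or sampling failure leaves a randomised patient with no baseline skin value and no replacement route

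*Protocol*

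**What the plan says.** Protocol section 10.3 states that the baseline measures "will be conducted as follows: 1) BMI, BP, waist-hip ratio 2) skin hydration", and continues as a numbered list to step 12. The part that matters reads "Randomization to 400mg oral AZD4017 twice daily or placebo 7) collection of IMP from pharmacy 8) obtain biopsy informed consent" and then "9) 2 x 3mm biopsies for 11"β-HSD1 activity and RNA-seq. After that come the 3-hour barrier-recovery reading (step 10), skin thickness (step 11, at the other site) and payment (step 12).

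Biopsy consent is separate from trial consent. Section 6.4.2 says "A separate Informed Consent Form will be attained prior to the skin biopsy procedure" and that the result is recorded as pass or fail. Section 14.3 places it at the visits where biopsies are taken: "The Skin Biopsy Informed Consent at Visits 1 and 4 can be received by a qualified member of staff".

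Section 6.5.2 makes randomisation the dividing line. Those who withdraw before it are screening failures. Those who withdraw after it "will be classified as withdrawals and will not be replaced".

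Section 3.1 defines the primary endpoint as skin 11β-HSD1 activity at baseline and day 28. Section 13.3 says that "the last valid measurement before study medication administration will be utilized as the baseline value". Section 8.2 starts dosing at Visit 1 without tying the first dose to completion of the baseline measures.

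**The concern.** The protocol has a workable rule for patients lost before allocation, but the Visit 1 order puts one foreseeable loss on the wrong side of it. The protocol itself allows for biopsy consent to fail, since it records pass or fail. In the order given, that answer comes only once the patient occupies one of the 30 randomised places. Nothing requires a successful baseline biopsy before randomisation, and no rule covers a patient who declines the biopsy but stays in the trial.

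One missed baseline biopsy visit removes the patient from several planned outputs: change from baseline in skin activity and the baseline/follow-up correlation (section 13.4.1), the baseline RNA-seq sample (9.2.3.8), and the first pair of wounds imaged at Visits 2 and 3 (9.2.3.7).

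A second, smaller gap concerns timing. The tablets are in the patient's hands from step 7, while the biopsies, the 3-hour barrier reading and skin thickness are still to come. The text does not say that these measures precede the first dose, yet section 13.3 would accept them as baseline only if they do.

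**Working it through.** **1. Is the list a sequence?** It is introduced as the way the measures will be conducted. It is numbered, it places the 3-hour reading well after the barrier disruption at step 3, and it ends with payment. It reads as the order of the visit.

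**2. The plan's own sample size (sections 6.2 and 13.9).** Inputs: 12 completers per arm and 20% drop-out.

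- 12 / (1 - 0.20) = 15 per arm, 30 in total. The stated figure is reproduced.
- Allowance per arm: 15 - 12 = 3, and expected drop-out is 15 × 0.20 = 3. The allowance is fully used, with no margin beyond the stated 20%.

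**3. What a missing baseline biopsy costs, by output.**

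| Planned output | Needs the Visit 1 biopsy? |
|---|---|
| Day-28 adjusted mean, the proof-of-concept criterion (13.4.1) | No. Adjustment is for gender, age and baseline HbA1c |
| Change from baseline and its between-group difference (13.4.1) | Yes |
| Correlation ρ between baseline and day 28, used in the factor (1 - ρ²) for future sample sizes (13.4.1) | Yes |
| Paired RNA-seq (9.2.3.8) | Yes |
| Healing of the Visit 1 wounds at days 2 and 7 (9.2.3.7) | Yes |

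Each such patient is 1 of 15 in an arm, or 6.7% of that arm, for the outputs marked yes.

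**4. How many patients?** The protocol gives no refusal or sampling-failure rate r. As an illustration only, assume r of 3%, 5% or 10%, independent between patients:

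| Assumed r | Expected among 30 (30r) | Chance of at least one, 1 - (1 - r)^30 |
|---|---|---|
| 3% | 0.9 | 60% |
| 5% | 1.5 | 79% |
| 10% | 3.0 | 96% |

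**5. Is there room to reorder?** Barrier integrity is tested by tape stripping at step 3, and the recovery reading three hours later is step 10. Randomisation, drug collection, biopsy consent and biopsy all fall inside that wait. Swapping their order uses the same window.

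**6. Timing of the first dose.** Section 8.2 fixes the day and section 13.3 fixes what counts as baseline. Section 10.3 has no dosing step at all. Together they neither place the first dose before the remaining baseline measures nor exclude it.

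**The case against.** Several points on the other side are sound and limit the finding.

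- A reader might infer that the deciding comparison is lost. It is not. Proof of concept rests on the adjusted day-28 mean, and baseline skin activity is not a listed covariate. A patient with only a day-28 biopsy still counts. Section 13.7 also plans multiple imputation, though it warns that this may prove impractical at this sample size.
- A reader might multiply the 80% retention by a further (1 - r) and conclude that the chance of reaching 12 completers per arm collapses. The protocol does not support that. Section 6.2 describes the 20% as post-randomisation drop-out, so refusals that end participation may already be inside it, and r itself is assumed.
- A reader might infer that section 6.5.2 expressly bars replacement. Its wording covers withdrawal, and declining one biopsy is not stated to be a withdrawal. What holds is that no replacement route is given.
- A reader might infer that some baselines will be taken after dosing. Step 7 is collection, not dosing, and steps 8 to 11 stand under the heading of baseline measures. The text leaves the possibility open; it does not show that it happens.
- Reordering cannot catch assay failures, because the samples are read only at the end of the trial (sections 9.1 and 11.10). It also does not affect the Visit 4 biopsy, which has its own consent.
- Patients receive the information leaflet, a telephone call and trial consent before Visit 1, so refusals at step 8 may be few.

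What remains is the order itself. It places refusals and sampling failures after allocation when they could be found before it.

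**Conclusion.** The finding holds in a limited form. Section 10.3 places randomisation and drug collection ahead of a separate consent that can fail and ahead of the procedure that supplies the primary endpoint's baseline. Patients lost at that step stay in the randomised set with no baseline skin value and no replacement route. They are lost to the change-from-baseline analysis, the correlation used to plan future trials, paired RNA-seq and the early wound-healing data, but not to the day-28 comparison.

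The number affected rests on a rate that the protocol does not give. What is certain is that 15 per arm carries no margin beyond the stated 20%. That the first dose follows the Visit 1 baseline measures is assumed by section 13.3 but not secured by sections 8.2 and 10.3. In a descriptive pilot this is minor to moderate: it is avoidable loss of information rather than bias in the main comparison.

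**What to change.** Reorder section 10.3 so that biopsy consent and both baseline biopsies come before randomisation and drug collection; the latter two can follow during the 3-hour barrier-recovery wait. Add a sentence to section 6.5.2 that a patient who declines, or from whom the baseline samples cannot be taken, is not randomised and is counted as a screening failure.

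Reconcile sections 8.2, 10.3 and 13.3 so that every Visit 1 measure used as a baseline, including skin thickness, is recorded as pre-dose, as section 13.3 already assumes. Skin thickness need not precede randomisation. It is measured at the other site, and moving it forward could add a journey between sites.

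The cost is small: no new procedure and no extra visit. A patient whose sampling fails may have had a biopsy attempt without being randomised. Slightly more invitations may be needed. The plan's figure is 30/(0.5 × 0.7) = 85.7, so 86. With the same assumed 3% to 10% lost at the biopsy step, and none of them already counted as ineligible, it becomes 30/(0.35 × 0.97) = 88.4 to 30/(0.35 × 0.90) = 95.2, so 89 to 96. Section 6.2 describes a pool of more than 45,000 patients.
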